**Fig. 1 Fig1:**
[figure not shown]
Proposed participant flow. TC+ KT, Kinesio taping + Tai Chi; TC+KTp, placebo Kinesio taping + Tai Chi; KT, Kinesio taping

### Sample size calculation

The sample size is calculated by the software G*Power 3.1.9 for Windows (G*Power© from University of Dusseldorf, Germany) [31]. The calculation of the sample size is regarded as the calculation of power, and its purpose is to observe whether there is a significant difference in the outcome indicators. This study consists of 3 groups and 3 measurements, the statistical power (1-β err prob) is 0.8, the type I error probability (α) is 0.05, the statistical analysis method is mixed-type analysis of variance, and the amount of effect obtained in the preliminary trial is 0.25, which is calculated by the software The sample size is 54 participants in total, with 18 participants in each group. At the same time, considering the 20% dropout rate and the equivalence between the groups, the sample size is 66 participants, and each group has 22 participants.

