### Study design

This article is a double-blind randomized controlled trial, recruiting 66 eligible college football players with FAI, randomly divided into 3 groups: TC+KT group, TC+KTp group, and KT group; the ratio is 1:1:1. Participants in the TC+KT group will receive 6 weeks of Tai Chi (3 times a week, 30 min each time) combined with Kinesio taping effect patch intervention; the TC+KTp group will receive 6 weeks of Tai Chi and muscle placebo technical intervention with internal effect patch; and the KT group will receive 6-week Kinesio taping effect patch intervention. Measurements will be taken at the baseline, mid-intervention period (4 weeks), and late intervention period (6 weeks) to check the maintenance of any intervention effects. The participant flow for this trial is presented in Fig. 1. The present protocol follows the Standard Protocol Items: Recommendations for Interventional Trials (SPIRIT) guidelines and fulfills the SPIRIT checklist (see Additional file 1).

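### Enrolling 66 players does not cover the stated 20% dropout: 52.8 would remain, against the 54 the plan requires

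*Protocol article*

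**What the plan says.** The Sample size calculation section of the protocol article describes a G*Power calculation for a mixed ANOVA with three arms, each assessed three times, at 80% power and a 5% significance level. For the size of the effect it relies on pilot data: "the amount of effect obtained in the preliminary trial is 0.25". From these inputs the section arrives at its requirement before any loss: "The sample size is 54 participants in total, with 18 participants in each group". Its allowance for loss follows, and here the total rises to 22 per arm: "considering the 20% dropout rate and the equivalence between the groups, the sample size is 66 participants". The inflation formula is not written out.

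The Study design section carries the same total forward, "recruiting 66 eligible college football players with FAI, randomly divided into 3 groups", with 1:1:1 allocation.

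**The concern.** A dropout rate is a share of the people enrolled. To keep a required number of completers, that number has to be divided by the share expected to stay. Multiplying it by one plus the dropout rate always gives too few, because the loss is then taken from the larger enrolled total. The figure of 66 looks like the product of multiplication.

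If so, the plan claims a protection it does not have: under its own dropout assumption, the enrolled number falls short of the number on which the stated 80% power rests. The claim would also be carried into the report of the results.

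**Working it through.** **Inputs, all from the Sample size calculation section:** 54 completers required, 18 per group; 20% dropout; 66 enrolled, 22 per group; equal groups.

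**Reproducing the plan's figure.** Multiplying by (1 + dropout):
- Per group: 18 × 1.2 = 21.6, rounded up to 22; 3 × 22 = 66.
- In total: 54 × 1.2 = 64.8, rounded up to 65, then to 66 for equal groups.

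Both routes reach 66 exactly.

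**The calculation that meets the requirement.** Dividing by (1 − dropout):
- In total: 54 / 0.8 = 67.5, so 68 without the equal-groups condition.
- Per group: 18 / 0.8 = 22.5, so 23; 3 × 23 = 69. As the plan asks for equal groups, 69 is the proper comparison.
- Check: 69 × 0.8 = 55.2, which is at least 54.

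**What 66 delivers.**
- At 20% loss: 66 × 0.8 = 52.8 in total and 22 × 0.8 = 17.6 per group, against 54 and 18. The shortfall is 1.2 players, or 0.4 per group.
- Largest loss that still leaves 54: 1 − 54/66 = 18.2%.
- If each player drops out independently with probability 0.2 (an assumption), the binomial chance of at least 54 completers is about 43% with 66 enrolled and about 70% with 69.

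**Effect on power.** This needs inputs that the article does not give. I read the effect of 0.25 as Cohen's f, take the group-by-time interaction as the test, and assume sphericity. With N players, 3 groups, 3 measurements and correlation ρ, the noncentrality is f² × N × 3 / (1 − ρ), on 4 and 2(N − 3) degrees of freedom, at α = 0.05.

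| Assumed ρ | Power at 52 | Power at 53 | Power at 54 |
|---|---|---|---|
| 0 | 0.679 | 0.689 | 0.699 |
| 0.19 | 0.782 | 0.791 | 0.800 |
| 0.3 | 0.845 | 0.853 | 0.861 |
| 0.5 | 0.950 | 0.954 | 0.958 |

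The row at 0.19 is the one in which 54 gives the stated 80% power. Across the whole range, going from 54 to 52 or 53 costs at most about two percentage points.

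**The case against.** The strongest reply is that the error is trivial. The shortfall is 1.2 expected players, a 20% dropout rate is a round planning guess, and the gap between 18.2% and 20% lies well within its uncertainty. This is right about size and keeps the point modest. It does not make the sentence true: total, rate and requirement stand side by side and do not fit.

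Second, the power loss depends on an unstated correlation. At 0.5 the interaction test would need only 36 players, so 52 or 53 would be ample; at 0, 54 itself gives only about 0.70. This stands: the correlation matters far more for power than the dropout step, so any power figure needs its assumed correlation beside it. The shortfall in numbers does not depend on it, because it takes 54 as the plan's own requirement.

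Third, the article shows no formula, so multiplication by 1.2 is an inference. That is also fair. What can be shown is that 66 agrees with multiplication and not with division into equal groups. However 66 was reached, it leaves 52.8.

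Finally, the larger target may be out of reach. The Trial status section has recruitment ending on October 30, 2021, and the article appeared on 2022-02-19. The Abstract moreover reports fifty-three players as randomised (20, 17 and 16). If that is the number enrolled, the trial was below 54 before any dropout, which limits the practical weight of 66 against 69. It does not correct the planning statement.

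**Conclusion.** The concern holds. Under the plan's own 20% dropout, 66 enrolled leave 52.8 completers and not 54; the total covers 18.2% loss, and the equal-groups total consistent with 20% is 69, three more than planned. This conclusion rests only on figures in the Sample size calculation section and on reading the dropout rate as a share of those enrolled. 

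The consequence is small: one recruit per group and about one to two points of power. The power part also rests on Cohen's f, the interaction test, sphericity and an assumed correlation. The statement should be corrected because it is wrong as written, although the error alone does not put the trial's conclusions in doubt.

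**What to change.** Replace the dropout sentence in the Sample size calculation section with one along these lines: *Enrolling 66 players (22 per group) leaves 54 evaluable with up to 18% dropout; at 20% dropout, 52 to 53 would remain.* Add the power at that number together with the correlation assumed, for example 0.78 to 0.79 at a correlation of 0.19. 

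If enrolment were still open, 69 (23 per group) would be the total consistent with 20%, and the Study design section would have to change with it; on the dates in the Trial status section this is unlikely to apply. 

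The cost is one sentence and a slightly less favourable statement of dropout protection. No trial procedure changes.

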### Setting and recruitment

This study will recruit FAI patients at the Football Academy of Beijing Sport University in China through WeChat, leaflets, and Weibo. The exercise intervention was independently supervised by 3 research assistants at this university, and data collection was carried out independently by other research assistants. Due to the impact of the new crown epidemic, this study will officially start recruiting in September 2021.

### Participant eligibility

The inclusion criteria of FAI are determined according to Delahunt (2010) [32]. The inclusion criteria are as follows: (1) repeated ankle sprains 2 times or more in the last year; (2) the most recent ankle sprain distance study> 1 month, the functional ankle joint feels out of control during activities; (3) Ankle Function Evaluation Questionnaire (AJ-FAT) score ≤ 26 points; (4) Ankle joint anterior drawer test and talus tilt test results are negative; (5) no fracture or lower limb medical history such as surgery; and (6) voluntary and signed informed consent. The exclusion criteria are as follows: (1) ankle sprain time < 1 month, (2) ankle pain at rest, (3) allergy to KT, (4) medical contraindications for physical activity (such as cardiovascular disease), and (5) the intervention cannot be persisted due to personal or other reasons. All subjects voluntarily and signed written informed consent before the intervention and were explained by the researchers on the research process and strictly followed the ethical standards of the Declaration of Helsinki.

### Randomization, allocation, and blinding

Random grouping is carried out by individual researchers. The generation of random sequence and random list are carried out by individual researchers through the SPSS (IBM. Version 20.0) software program. This is done on subjects who have signed the “Informed Consent.” Make sure the group is hidden. Participants were randomly divided into 3 groups: TC+KT (*n* = 20), Tai Chi combined with Kinesio taping patch intervention; TC+KTp (*n* = 21), Tai Chi and Kinesio taping patch placebo technical intervention (*n* = 21); and Kinesio taping patch intervention which was performed alone.

In this trial, the assessments and treatments were performed by different therapists. The evaluator was blinded to the subject assignment. All the intervention procedures were performed by the same physiotherapist who had experience in the field of sports physical therapy. Both the physiotherapist and the participants were blinded to the purpose of the study. In addition, a different researcher, blinded to the object of the study, carried out the data analysis.

### Intervention

#### Intervention plan

The three different interventions lasted for 6 weeks. During this period, they normally participated in the usual football courses (i.e., 2 times a week, 90 min each time, 1 game on weekends). Subjects in the TC+ KT and KT groups, in both ankles, had KT functional correction taping technology. The KTp+ TC group used placebo technology (tension-free) KT. The TC training of subjects in the TC+ KT and KTp+ TC groups focused on lower limb posture control.

#### Kinesio taping

The functional correction technique of Kinesio taping effect sticking is a kind of Kinesio taping effect sticking technology [33]. The width of the patch is 5 cm, the thickness is 0.05 cm, with 70% tension, and it is pasted on both ankles [34]. The method of sticking is as follows: the subject lies on his back with the toes facing up, and the patch goes across the metatarsal bones from the outside of the instep to the inside without applying tension. Then, reach the lateral malleolus through the sole of the foot with 70% tension, traverse the lateral ligament of the ankle joint, extend up to the end of the gastrocnemius tendon, and stick the remaining part in the middle of the gastrocnemius without tension. The calculation of the tension percentage is based on the length of the KT, and we spread on the paper as the base point (0%), stretched the patch with the maximum tension, and measured its length (100%). Therefore, the tension required for KT in this study is 70%, that is, the difference between the maximum usable tension required by the patch, and the base point length is 70% [35]. After the taping was completed, the subjects were asked whether there was pain, and a half squat was performed to compare the pain. If there is no pain, the tape is completed.

Ankle joint injury is usually a strain of the lateral ligament. Therefore, the purpose of KT functional correction technology is to make the ankle joint valgus and prevent varus, so as to prevent ankle joint sports injuries [36].

#### Placebo Kinesio taping

The pasting of the patch is the same as before, but the tension of the patch is 0%. The patch is only attached to the subject’s ankle without any stretching. Both functional correction tape and placebo tape were applied to both ankles of the subjects, and the tape was taped once every 5 days [37]. If the subject discovers any skin allergies when changing KT, they will be excluded from the study.

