### Safety measurements

Any unexpected adverse events that occurred during the 6-week intervention period will be reported to the research assistant, and the causal relationship between Tai Chi exercises and Kinesio taping effects will be evaluated. If a serious sports injury or other adverse event occurs, the research assistant will immediately report to the project leader and the Sports Science Ethics Committee of Beijing Sport University; they will decide whether the participant need to withdraw from the study.

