### Statistical analysis

Statistical analysis was performed through the statistical package for social sciences software (The Statistical Package for Social Sciences, SPSS 23, SPSS Inc., Chicago, IL, USA). The normal distribution of variables is carried out by Shapiro-Wilk. Descriptive statistical analysis is described in the form of mean ± standard deviation. Through mixed two-factor multivariate analysis of variance, the effects of intervention groups (such as TC + KT, KTp + TC, KT) and time (such as before, during, and after intervention) were analyzed by reasoning. Multiple comparisons were made through post hoc analysis and Bonferroni correction for the variables of the variance analysis significance results. According to Cohen’s method, the effective amount is calculated. This method divides the effect amount into large (0.8), medium (0.50–0.79), and small (0.20–0.49) [45]. The alpha level for all tests is set to 0.05. A single-factor multivariate analysis of variance was used to compare the subjects’ baseline age, height, weight, and leg length data to explore whether the groups are homogeneous.

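### Randomised players who develop a skin allergy to the tape are excluded from the study, with no separation between stopping the tape and leaving the trial

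*Protocol article*

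**What the plan says.** The rule stands in the protocol article under Placebo Kinesio taping: "If the subject discovers any skin allergies when changing KT, they will be excluded from the study". The same paragraph sets the renewal interval ("the tape was taped once every 5 days") and makes clear that it concerns both kinds of tape: "Both functional correction tape and placebo tape were applied to both ankles of the subjects". The tension is 70% for the functional correction technique (section Kinesio taping) and 0% for placebo.

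Three other places bear on the point:

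- Participant eligibility lists known tape allergy as exclusion (3). Exclusion (5) reads "the intervention cannot be persisted due to personal or other reasons", with no statement of when it applies.
- Safety measurements treats serious injury or another adverse event differently. The event is reported to the project leader and the ethics committee, and "they will decide whether the participant need to withdraw from the study".
- Outcome assessment and Data collection schedule tests at baseline, week 4 and week 6. Statistical analysis compares arms over time ("Through mixed two-factor multivariate analysis of variance").

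**The concern.** A skin reaction found at a tape change arises after allocation and is a response to the allocated treatment. Removing the player for it makes membership of the compared groups depend on how treatment was tolerated, and randomisation no longer guarantees that those who remain are comparable.

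The rule also treats two decisions as one. Whether tape continues is a matter of clinical handling. Whether the player is still tested at weeks 4 and 6, and counted in the allocated arm, is a matter of design. As written, a reaction settles both. If exclusion ends the assessments, the outcomes are not collected, and no later analysis plan can bring them back.

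**Working it through.** The plan states no figure on this point. The check is mainly a comparison of sections, with a little arithmetic.

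**1. Does the rule act after randomisation?** The intervention lasts 6 weeks (Intervention plan), which is 6 × 7 = 42 days, and tape is renewed every 5 days. 42 / 5 = 8.4. If the first tape goes on at day 0 (my assumption), there are eight renewals, on days 5 to 40. All of them fall after allocation, because the type of tape depends on the arm.

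**2. Which outcomes are at risk?** Week 4 is day 28. Five renewals precede it (days 5, 10, 15, 20, 25) and three follow it (days 30, 35, 40). If exclusion ends assessment, a reaction found at one of the first five costs both follow-up tests. One found at the last three costs the week 6 test.

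**3. Is it only the entry criterion restated?** No. Exclusion (3) concerns allergy known at entry. The taping rule concerns allergy found at a tape change, in a player who has already passed exclusion (3).

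**4. Does it remove the player or only the tape?** It removes the player, and automatically. After a serious event, by contrast, withdrawal is left to a decision (Safety measurements). No sentence in the article says that a player excluded for allergy is still assessed.

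**5. Which arms?** I read it as all three. The rule sits under the placebo heading, but the sentence before it covers both kinds of tape. Site and renewal interval are the same; tension is 70% in two arms and 0% in the third.

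**6. What could this do to a contrast?** In arm *j*, let *p_j* be the fraction removed and *d_j* the mean outcome of retained players minus that of removed players. The full-arm mean is (1 − *p_j*) × retained mean + *p_j* × removed mean, so

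retained mean − full-arm mean = *p_j* × *d_j*.

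For arms A and B the contrast therefore shifts by

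*p_A d_A* − *p_B d_B*.

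This is zero if nobody reacts, if reacting is unrelated to outcome, or if the two products are equal. Otherwise it can take either sign. The article gives neither *p* nor *d* for any arm, so I put no number on it.

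**7. Does the dropout allowance deal with it?** No. Sample size calculation raises 54 players to 66, or 66 − 54 = 12 extra, for a 20% dropout rate. That protects the number of players, not the comparability of those who remain.

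**The case against.** The strongest reply has two parts, and both largely stand.

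First, the article names no analysis set, and an analysis set may properly be left to a statistical analysis plan or full protocol that is not shown. That silence is no fault. The taping rule, however, is not silence: it is a stated exclusion that may stop data collection before any analysis set is applied.

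Second, all three arms wear tape in the same place on the same schedule, known allergy is screened out, and nothing in the article links tension to skin reaction. The numbers affected may be small and balanced. Unequal loss is therefore possible but not demonstrated.

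A reader might also draw stronger conclusions that the document does not support:

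- **That non-adherers are removed after randomisation.** Exclusion (5) is an eligibility item. It can be read as inability foreseen at screening, and no section applies it later. The Discussion mentions adherence to Tai Chi as a limitation, not as a ground for removal.
- **That tape reactions go unreported.** Safety measurements begins with unexpected events but goes on to cover other adverse events, and requires an assessment of causal relationship that includes the taping. Nothing says that an excluded player's reaction is left out.
- **That the differing group sizes show the rule at work.** The Abstract gives 20, 17 and 16. Randomization, allocation, and blinding prints 20, 21 and a further 21. If the second 21 is the KT arm, the differences are 0, 4 and 5. The article does not say that one set is those randomised and the other those retained, and it attributes no loss to allergy.

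**Conclusion.** The point holds for the allergy rule alone. The article fixes a post-randomisation exclusion, triggered by a reaction to study treatment, that does not distinguish stopping tape from leaving the trial. This rests on two readings: that exclusion ends the week 4 and week 6 assessments, and that the rule covers all three arms. The wording favours both.

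The size and direction of any bias are unknown, because no reaction rates and no outcomes of affected players are given. It would also be too strong to say that the comparison is confined to players who tolerated and adhered to their arm: no section states such a rule. The change is still worth making, because it uses tests already scheduled and removes an avoidable departure from analysis as randomised.

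**What to change.** Replace the exclusion clause under Placebo Kinesio taping with wording to this effect: a player with a skin reaction at a tape change remains in the trial, is assessed at weeks 4 and 6 where willing, and is analysed in the allocated arm. A set without such players may be used only as a sensitivity analysis. Clinical handling of the reaction, including what happens to the tape, is not altered by this change.

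Trial status puts the end of procedures in December 2021. If follow-up has ended, report every such exclusion by arm and reason, and analyse all available data as randomised. A repeated-measures ANOVA restricted to complete records would drop players with a missing visit, so that analysis needs a method that keeps partial records.

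As a secondary clarification, state that exclusion (5) applies to inability known before randomisation.

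The cost is a sentence or two of protocol text and the attendance of affected players at tests already in the schedule. The downside is that the estimated effect may be slightly diluted by including players who stopped part of their treatment.

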#### Tai Chi

The intervention actions of Tai Chi are selected from the 24 styles of Tai Chi [38]: knee-knee and stance, inverted brachial, clouded hand, left-right and lower-independence (including footsteps, piercing palms and golden rooster independence), and jade girl shuttle and 5 movements, knee and stance, inverted brachial, clouded hand, left and right golden rooster independent, and jade girl shuttle, including single foot support, single foot left support, single foot right support, left support, right heel contact with the ground, the right support, left heel contact with the ground, left support, right toe touches the ground, right support, left toe touches the ground, and a total of 7 support methods and different movement directions (front and back, left and right, up and down, front left, front right). These actions are mainly to control the balance and posture of the lower limbs of the body. In addition to the normal class and training, the subjects intervened in the reference guide [39] and adjusted according to the characteristics of the subjects and practiced 3 times a week, each for 30 min. The intervention is divided into two stages: learning in the first 2 weeks and improvement in the next 4 weeks. Each exercise in the first 2 weeks includes 5 min of warm-up, 20 min of learning new movements, and 5 min of stretching. The last 4 weeks include 5 min of warm-up, 20 min of repetitive exercises, and 5 min of stretching.

